## Abstract

**Background:**

In 2020, 1.4 and 2.3 million new cases of prostate cancer and breast cancer respectively were diagnosed globally. In the UK, prostate cancer is the most common male cancer, while breast cancer is the most common female cancer. Engaging in physical activity (PA) is a key component of treatment. However, rates of PA are low in these clinical populations. This paper describes the protocol of *CRANK-P* and *CRANK-B*, two pilot randomised controlled trials, involving an e-cycling intervention aimed at increasing PA in individuals with prostate cancer or breast cancer respectively.

**Methods:**

These two trials are single-centre, stratified, parallel-group, two-arm randomised waitlist-controlled pilot trials in which forty individuals with prostate cancer (*CRANK-P*) and forty individuals with breast cancer (*CRANK-B*) will be randomly assigned, in a 1:1 allocation ratio, to an e-cycling intervention or waitlist control. The intervention consists of e-bike training with a certified cycle instructor, followed by the provision of an e-bike for 12 weeks. Following the intervention period, participants in the e-bike condition will be directed to community-based initiatives through which they can access an e-bike. Data will be collected at baseline (T0), immediately post intervention (T1) and at 3-month follow-up (T2). In addition, in the intervention group, data will be collected during the intervention and follow-up periods. Quantitative and qualitative methods will be used. The primary objectives are to determine effective recruitment strategies, establish recruitment and consent rates, adherence and retention in the study, and determine the feasibility and acceptability of the study procedures and intervention. The potential impact of the intervention on clinical, physiological and behavioural outcomes will be assessed to examine intervention promise. Data analyses will be descriptive.

**Discussion:**

The findings from these trials will provide information on trial feasibility and highlight the potential of e-cycling as a strategy to positively impact the health and behaviour of individuals with prostate cancer and breast cancer. If appropriate, this information can be used to design and deliver a fully powered definitive trial.

**Trial registration:**

CRANK-B: [ISRCTN39112034]. CRANK-P [ISRCTN42852156]. Registered [08/04/2022] https://www.isrctn.com.

**Supplementary Information:**

The online version contains supplementary material available at 10.1186/s40814-023-01293-3.

## Background

Prostate cancer (PCa) and breast cancer (BC) are two of the most common cancers globally [1] with 1.4 and 2.3 million new cases diagnosed in 2020 respectively [2]. Improvements in clinical diagnosis and treatment are leading to rising survival rates, and more individuals are living longer with these cancers [3–5]. However, this growing population of cancer survivors experience a range of physical and psychological side effects associated with their cancer and/or treatment and are more likely to suffer from other chronic diseases [6–8]. As such, there is growing interest in developing lifestyle interventions that can help reduce side effects, improve quality of life and prevent further morbidity [9, 10].

Engaging in physical activity (PA) has been identified as having numerous health benefits in cancer survivors [11, 12]. Among PCa survivors, engagement in moderate to vigorous physical activity (MVPA) throughout the cancer journey has been found to lead to improvements in quality of life, physical functioning and reduced cancer-specific fatigue [13–15], while among BC survivors, PA engagement has been associated with improvements in self-esteem and quality of life [16]. Furthermore, higher levels of post-diagnosis PA are associated with reduced risk of all-cause mortality and PCa or BC-specific mortality compared to those who engage in low levels of PA [17–23]. It is therefore recommended that cancer survivors engage in PA during and after cancer treatment [24, 25]. In the UK, NICE now recommend supervised exercise as part of PCa treatment [26]. However, clinical teams are rarely able to deliver targeted PA information or supervised exercise programmes to PCa patients due to time constraints and feeling under qualified to promote or deliver such a programme [27]. Within BC treatment, the promotion of PA is not currently an integrated part of routine care. A UK survey found that around half of oncologists and surgeons do not routinely discuss PA with their BC patients [28]. Furthermore, BC patients report not getting information and/or PA recommendations from healthcare professionals during and after treatment [29].

The lack of PA promotion during treatment is concerning as rates of PA are low among cancer survivors [30–32], and many individuals with PCa and BC fail to meet PA guidelines [33] with self-reported reductions in PA levels following diagnosis and during treatment [34]. Reported barriers to engaging in PA among cancer patients relate to both treatment, including fatigue, pain, a lack of motivation and a decreased confidence to engage in PA and general PA barriers including age-related physical decline and lack of time [34–37]. As such, finding novel ways to increase PA in cancer patients, which increases PA confidence, is a priority.

Electrically assisted bicycles (e-bikes), also known as pedelecs, have been highlighted as a means through which to increase PA in inactive and older adults [38]. E-bikes provide gradated electrical assistance only when the rider is pedalling, through sensors which detect pedalling speed and force. This assistance enables increased speed and reduced physical exertion which is believed to lead to the high level of enjoyment repeatedly reported when e-cycling [39–48] and are likely to be the main motivators that have led to the increased popularity of e-bikes particularly among inactive and older-aged adults [49–51].

Despite the increased assistance, riding an e-bike provides PA of at least a moderate intensity [52–55] and can lead to improvements in cardiorespiratory fitness [55], glucose control [56] and health-related quality of life [57] in inactive or older adults. Among individuals with type 2 diabetes mellitus, e-cycling has been shown to be performed at a moderate intensity with potential for improving glucose control, health-related quality of life and cardiorespiratory fitness [58]. These positive findings suggest that exploring the use of e-bikes as a means of increasing PA in other clinical populations is warranted, including individuals with cancer, a research area yet to be explored. Given the lack of current research, there is insufficient evidence to support full-scale randomised controlled trials (RCT). Rather, pilot RCTs are needed to determine trial feasibility and to provide key information needed for the design of full-scale definitive trials, if warranted.

### Study aims and objectives

The *primary* aim of this study is to test the feasibility of conducting two pilot randomised controlled e-cycling interventions among individuals with PCa (*CRANK-P*) and BC (*CRANK-B*). Two pilot RCTs will be conducted because these different clinical populations have different recruitment and treatment pathways. However, the primary aim of the two trials is the same and will be addressed by answering the following questions:Can individuals with PCa/BC be recruited to an e-cycling trial?Are participants’ willing to be randomised, do they remain in the study and adhere to the intervention and data collection methods, and what are the rates of harmful events?Can the intervention be implemented as intended?Are the intervention and study procedures acceptable to participants, instructors and the clinical team?What are participants’ experiences of e-cycling?

While the pilot RCTs will be insufficiently powered to statistically examine the effectiveness of the intervention on outcomes, they provide an opportunity to investigate the potential promise of the intervention. As such, the *secondary* aim is to examine the association between the intervention and outcome measures to determine intervention promise. To address this aim, the following question will be answered:6.What is the potential effect of the intervention on a range of individual health and behavioural outcomes?

## Methods

### Study design and setting

The proposed trials are single-centre, stratified, parallel, two-arm pilot randomised control trials, whereby individuals with PCa (*CRANK-P*) or BC (*CRANK-B*) will be randomly assigned to either an e-cycling intervention or a standard-care waitlist control. Forty individuals will be recruited for each trial and randomised in a 1:1 allocation ratio to the two study arms. The trials will be conducted in the city of Bristol, England. Recruitment began in June 2022. Measures will be collected predominantly at baseline (time 0 (T0)), immediately following the intervention period (T1) and at 3-month follow-up (T2). In addition, data will be collected in the final week of the e-cycling intervention and follow-up period (PA and travel behaviour) and throughout the intervention and follow-up period (e-cycling time and distance). Figure 1 shows the study flow diagram for the two trials. Reporting of this protocol is according to the SPIRIT checklist (Additional file 1). CRANK-P has been approved by the NHS Health Research Authority Dulwich Research Ethics Committee (REC: 22/LO/0036), and CRANK-B has been approved by the Nottingham Research Ethics Committee (REC: 22/EM/0010). Both trials are sponsored by the University of Bristol. Any amendments to the protocol will be authorised by the sponsor and submitted to the appropriate REC and HRA for approval.

**Fig. 1 Fig1:**
[figure not shown]
**a** Flow diagram of the CRANK-P trial. **b** Flow diagram of the CRANK-B trial

### Recruitment

The two trials will use different recruitment pathways. These are detailed below.

#### CRANK-P

Men who are diagnosed with PCa residing in the Bristol area and who attend the Bristol Urology Institute, North Bristol NHS trust, will be invited to participate. The study will aim to recruit 20 individuals at the start of their cancer journey (i.e. soon after receiving a PCa diagnosis) and 20 individuals who have completed their primary cancer treatment (i.e. after surgery, systemic therapy or radiation therapy) to determine the most appropriate time to recruit individuals during treatment. Patients will be highlighted as potentially eligible at the weekly multidisciplinary team meeting where all patients with a cancer diagnosis are discussed.

For individuals being recruited at diagnosis, initial contact will take place at their diagnosis appointment. At this appointment, patients are informed of their PCa diagnosis by their cancer nurse specialist (CNS). The research will be introduced to the patient at the end of the appointment by saying “We are conducting lifestyle research within the department, are you willing for a research nurse to call you to discuss this further?” This contact will take approximately 1 min. If the patient says yes, they will be provided with an information sheet, and their contact details will be passed on to the urology research nurse team. Men will receive a second opportunity to be informed about the study when they see consultant members of the clinical team (urology/oncology) to discuss their treatment options using the same approach method as above.

For individuals recruited at the end of their primary treatment, initial contact will take place at the patient’s post intensive treatment appointment. At this appointment, patients meet with a CNS or their consultant to discuss their cancer and future treatment. The research will be introduced in the same manner as for those approached at diagnosis, and those who are willing to be contacted will be provided with an information sheet, and their contact details will be passed on to the urology research nurse team.

Individuals who later contact the department interested in participating in the study will have an opportunity to ask questions, an information sheet will be sent by email or in the post, and they will be asked whether they agree to be contacted by a member of the research nurse team after they have had time to read the information sheet.

The urology research nurses will contact individuals who have expressed an interest in participating to confirm eligibility. If eligibility is confirmed, the research nurses will pass on the individual’s contact details to the university research team. All individuals deemed eligible for the study at this point will be invited for baseline testing. Table 1 outlines the enrollment and assessment schedule for the two pilot RCTs.

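### CRANK-P compares two times to recruit, but men at diagnosis get up to two scripted approaches and men after treatment are described as getting one, so uptake mixes timing with number of approaches

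*Protocol article*

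**What the plan says.** The Recruitment section for CRANK-P sets two targets: "The study will aim to recruit 20 individuals at the start of their cancer journey" and "20 individuals who have completed their primary cancer treatment". It gives one reason for the split: "to determine the most appropriate time to recruit individuals during treatment".

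The approach schedules are then described separately.

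- **Diagnosis group, first approach:** "For individuals being recruited at diagnosis, initial contact will take place at their diagnosis appointment". The cancer nurse specialist makes it with a short scripted question.
- **Diagnosis group, second approach:** "Men will receive a second opportunity to be informed about the study when they see consultant members of the clinical team". This is the visit on treatment options, and the approach method is the same.
- **Post-treatment group:** "initial contact will take place at the patient’s post intensive treatment appointment". A nurse specialist or a consultant makes it, and "The research will be introduced in the same manner as for those approached at diagnosis". No second approach is described.

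Men who contact the department later on their own initiative are handled in one paragraph that is not limited to either group.

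The recruitment log is described at the end of the CRANK-B recruitment text and covers both trials. For CRANK-P the nurse specialist records how many patients attend, how many are potentially eligible and how many of those decline contact. Refusals and any reasons reach the research team only as a count. No breakdown by first or second approach is stated. The Quantitative analysis section reports recruitment as frequencies and percentages.

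**The concern.** The timing question is the stated purpose of the 20 + 20 split. Because the targets are equal, the planned numbers recruited do not themselves tell the two times apart. On the recruitment side, what can differ is uptake per eligible man and how quickly each set of places fills.

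Both measures depend on how often a man is asked. The script is the same at each contact, so the number of approaches is a clear procedural difference between the groups on top of timing. The diagnosis figure is cumulative over two visits, and the post-treatment figure comes from one. The second approach at diagnosis is also made by a consultant and at a later visit.

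If yield turned out higher at diagnosis, the team could not tell from cumulative uptake whether a definitive trial should recruit early or simply ask twice. If approaches are not separated on the log as they happen, they may not be separable afterwards, because refusals are passed on only as a number.

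**Working it through.** The plan states no uptake figure by time point, so there is nothing to reproduce. The check asks how large a gap the schedule alone could create if men were equally willing at both times.

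**Inputs**

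- Number of approaches: up to two at diagnosis, one described after treatment (Recruitment, CRANK-P).
- Target per time point: 20 (same section).
- Acceptance at a first approach, p = 0.20 at both times. This is an assumption. It borrows the roughly 20% in the Sample size section, but that figure is an anticipated overall recruitment rate, whereas the scripted question asks only for permission to call. Eligibility checks, the baseline visit and consent come later.
- Acceptance at a second approach among men who declined the first, q = 0, 0.05, 0.10 or 0.20. This is also an assumption. The top value treats men who have just declined as being as willing as men never asked.

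**Formulas**

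- Uptake at diagnosis: U = p + (1 − p) × q. Uptake after treatment: p.
- Men approached to fill 20 places: 20 / U at diagnosis, and 20 / 0.20 = 100 after treatment.
- Standard error of the difference: √[U(1 − U)/n₁ + p(1 − p)/n₂], with n₁ = 20 / U (rounded) and n₂ = 100.

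**Results for p = 0.20**

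| q | U at diagnosis | After treatment | Spurious gap | Men approached at diagnosis | SE of difference | Gap / SE |
|---|---|---|---|---|---|---|
| 0 | 20% | 20% | 0 points | 100 | 5.7 points | 0 |
| 0.05 | 0.20 + 0.80 × 0.05 = 24% | 20% | 4 points | 83 | 6.2 points | 0.6 |
| 0.10 | 0.20 + 0.80 × 0.10 = 28% | 20% | 8 points | 71 | 6.7 points | 1.2 |
| 0.20 | 0.20 + 0.80 × 0.20 = 36% | 20% | 16 points | 56 | 7.6 points | 2.1 |

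For the last row: SE = √(0.36 × 0.64/56 + 0.20 × 0.80/100) = √(0.00411 + 0.00160) = 0.076.

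**Sensitivity to p.** Taking q = p as the upper limit, p = 0.10 gives 0.10 + 0.90 × 0.10 = 19% against 10% (9 points). With p = 0.30 it gives 0.30 + 0.70 × 0.30 = 51% against 30% (21 points).

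**After the fix.** If both groups are counted at the first approach only, equal willingness of 20% gives 20% in each, and the gap due to the schedule is 0.

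**The case against.** The strongest reply is that uptake is only part of the evidence. The protocol asks for the most appropriate time, which need not be the time of highest acceptance. It also collects retention, adherence, follow-up completion and reasons for declining, and it interviews the clinical team about recruitment and patients' receptiveness. This stands. A reader might infer that uptake alone decides the timing question, or that the schedule will send the definitive trial to the wrong recruitment point. The documents do not support either reading.

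Second, a reader might infer that men after treatment are limited to one invitation. The text describes one but sets no cap. The flow diagram in Fig. 1a is not available here, and self-initiated contact is not restricted to either group. So one approach is what the procedure describes, not a stated limit. Likewise, men at diagnosis get up to two approaches.

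Third, the diagnosis group is defined as a period soon after diagnosis, and a treatment-options visit can fall within it. Comparing whole pathways as they would run in practice is a legitimate feasibility aim. This also stands, and it is why first-approach uptake should not replace cumulative uptake: used alone, it would narrow the group to the visit at which the man is told his diagnosis. But a comparison of pathways cannot attribute a difference to timing.

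Fourth, timing is not randomised. The groups also differ in clinical situation and in who makes the approach, so this was never a controlled contrast of timing, and the analysis is descriptive. That is true, but it does not excuse an avoidable extra difference that can be separated by recording it.

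Finally, the log's layout could be settled in the full protocol. That is possible. The unequal schedule, however, is in the procedure as written, and separation by approach matters only because of it.

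**Conclusion.** The point holds in a limited form. As written, the CRANK-P procedure sets cumulative uptake over up to two approaches at diagnosis against uptake from the single approach described after treatment. Uptake per eligible man and speed of filling places are therefore confounded with the number of approaches.

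On the assumptions shown, the spurious gap lies between 0 and 16 percentage points when first-approach acceptance is 20%. It vanishes only if nobody who declines first accepts later. Against a standard error of about 6 to 8 points, the middle scenarios are within ordinary sampling noise and only the upper end clearly exceeds it. These figures illustrate the mechanism and do not predict the result, because neither acceptance rate is given in the protocol.

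The randomised comparison of e-cycling with waitlist is unaffected, and so is each pathway's own descriptive recruitment rate. The change is still worth making, because timing is the stated reason for the split and the remedy costs very little.

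**What to change.** Record for each man, in anonymous tallies, the appointment at which each approach was made and the appointment at which he agreed to be contacted. This must cover approaches made by consultants as well as by the nurse specialist.

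Report for each time point, with 95% confidence intervals:

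1. first-approach uptake, as the like-for-like comparison of timing;
2. cumulative uptake over the pathway as delivered.

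Show the added yield of the treatment-planning visit as a separate line. State that a difference in cumulative uptake will not be attributed to timing alone, and read both figures beside the retention, adherence, reasons-for-declining and interview evidence.

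The cost is one extra log field and a few descriptive figures, with no change to how patients are approached. The protocol says recruitment began in June 2022, so the field is useful only for approaches made once it is in place. If earlier approaches cannot be separated, the report should say so.

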**Table 1 Tab1:**
[figure not shown]
CRANK-P and CRANK-B SPIRIT diagram displaying study recruitment and measures schedule

*Pre-screening and eligibility screening will occur at the Bristol Oncology Centre for CRANK-P and Bristol Breast Care Centre for CRANK-B, T = time, M = month

#### CRANK-B

Individuals who are diagnosed with BC residing in the Bristol area and who attend the Bristol Breast Care Centre, North Bristol NHS trust, will be invited to participate. The study will aim to recruit individuals after their primary cancer treatment (i.e. following completion of surgery, systemic therapy and/or radiation therapy).

At the holistic needs assessment, which occurs after primary cancer treatment, the research will be introduced to the patient by the MacMillan key worker who will ask “We are conducting lifestyle research within the department, are you willing for a research nurse to call you to discuss this further?” If the patient says yes, they will be given a study information sheet, and their contact details will be passed on to the breast care research nurse team.

Individuals who later contact the department interested in participating in the study will have an opportunity to ask questions, an information sheet will be sent by email or in the post, and they will be asked whether they agree to be contacted by a member of the research nurse team after they have had time to read the information sheet.

The BC research nurses will contact individuals who have expressed an interest in participating to confirm eligibility. If eligibility is confirmed, the research nurses will pass on the individuals contact details to the university research team. All individuals deemed eligible for the study at this point will be invited for baseline testing.

The CNS (CRANK-P) and MacMillan key worker (CRANK-B) will keep a record of the number of patients attending the appointments, the number who are deemed potentially eligible and the number of potentially eligible patients who do not wish to be contacted to discuss the research. Individuals who are deemed eligible but who are not interested in participating will be invited to share their decision not to participate if they feel comfortable doing so with the clinical team. The number of individuals not wanting to be contacted and associated reasons, if provided, will be collated and passed on to the research team as a number, so that each refuser remains anonymous, and confidentiality is maintained.

